### 2.3. Participants and Setting

Patients will be community dwelling adults with insomnia and established MCI or mild dementia attending a large university-hospital-associated outpatient memory clinic affiliated with the Mercy University Hospital in Cork City in the south of Ireland called the Regional Specialist Memory Clinic (RSMC), Cork, Ireland.

#### 2.3.1. Inclusion Criteria

Participants will be deemed eligible for inclusion provided they are aged 50 years or older and meet criteria for insomnia, defined as a score of ≤16 on the Sleep Condition Indicator (SCI) [38] (an 8-item measure scored from 0 to 32 points, with scores ≤ 16 suggesting insomnia), aligned with DSM-5 diagnostic criteria. Eligible participants must have a prior clinical diagnosis of MCI or mild dementia made by an attending physician, with dementia staged as mild (based on the Reisberg Functional Assessment Staging Tool stages 3 or 4 [39]) and MCI defined according to Petersen’s criteria [40]. Cognitive status will be further confirmed by the Mini-Mental State Examination (MMSE), a widely-used test of cognition which is scored from 0 to 30 points, with higher scores indicating better cognition [41] and the Clinical Dementia Rating (CDR), which is a commonly-used clinician rated measure of global symptom severity and burden in persons with cognitive impairment [42]. To participate, those with MCI/mild dementia must score ≥18 on the MMSE and ≥0.5 to 1.0 on the CDR. Participants must have access to the internet via a computer, tablet, or smartphone for the duration of the intervention, and possess sufficient physical and sensory capacity (including vision and hearing ability) to engage with the intervention, as determined by the study team. Digital literacy will be assessed and supported separately, see above. Additional inclusion criteria include being English-speaking as the Sleepio digital CBT-I program is only currently available in English, living in the community (i.e., not in a nursing home or other institution), and having the capacity to provide informed written consent as judged by the principal investigator.

#### 2.3.2. Exclusion Criteria

Participants will be excluded if they have a diagnosed sleep disorder other than insomnia, as defined by the International Classification of Diseases. Individuals who have received CBT-I within the previous six months will also be excluded. To ensure inclusion of participants with mild stage impairment (MCI or dementia), those with an MMSE score <18/30 at enrolment will be ineligible. Exclusion criteria further include severe depression (e.g., requiring hospital admission within the preceding 12 months or recent psychiatric outpatient review), as well as unstable depression, anxiety, or panic disorders, defined by changes in psychotropic medication within the preceding three months. Individuals with other major neuropsychiatric conditions (including psychosis, schizophrenia, bipolar disorder or other mania disorder, and epilepsy, or other seizure disorders), or those with ongoing substance or alcohol misuse, will also be excluded. Additional exclusions include significant physical, sensory, or medical conditions that may impede participation, as judged by the principal investigator, as well as planned surgery or hospitalisation during the study period. Participants deemed medically unfit to continue by the investigator will not be enrolled. Finally, individuals who have had recent (within three months) changes in medications that may affect sleep or cognition, including hypnotics, anxiolytics, antidepressants, antipsychotics, cognitive enhancers (e.g., cholinesterase inhibitors or memantine), stimulants, decongestants, opioid analgesics, β-blockers, certain pulmonary medications, or melatonin, will be excluded.

### 2.4. Recruitment

Consecutive patients attending the RSMC Cork will be screened for eligibility using continuous recruitment during the study window. Patients who meet the predefined inclusion criteria will be invited to participate in this feasibility study, in line with recommendations for pilot trials. Eligibility screening will be undertaken by the principal investigator or a delegated member of the research team, all of whom are experienced clinicians working within the participating memory clinics. The target of the study is to recruit a total of 30 patients over a six-month recruitment period. A formal sample size calculation has not been undertaken, as the primary objective is to assess feasibility outcomes; however, this sample size is considered adequate to evaluate key parameters such as recruitment, retention, and intervention adherence, and to inform the design and sample size estimation of a future definitive RCT. If available and deemed by the study investigators to be required, study partners, defined as family members or close friends, will also be recruited to provide support to participants and to facilitate engagement with the intervention throughout the study period.

### 2.5. Consent Process

Fully informed and written consent will be required from each participant before enrolling them in the study. Capacity to provide informed consent will be assessed and confirmed by an attending consultant physician, ensuring that all participants have the ability to understand the nature, purpose, and potential risks and benefits of the research. Only individuals deemed capable of providing valid consent will be included. Where applicable, additional written consent will also be sought from study partners, defined as caregivers, family members, or close friends, who are willing to participate in a supportive role. These individuals will be informed about their role within the study and their involvement will be contingent on their voluntary agreement to participate. All study procedures will be conducted in accordance with applicable data protection legislation, including the European Union’s General Data Protection Regulation (a.k.a. GDPR), with appropriate measures in place to ensure the confidentiality, secure storage, and controlled access of all personal data.

### 2.6. Outcome Measures

These feasibility thresholds will be predefined a priori based on published recommendations for pilot and feasibility studies together with adherence data from comparable digital behavioural interventions.

#### 2.6.1. Primary Outcomes

Recruitment of the target number of 30 participants during a six-month study period.Retention of ≥70% of participants throughout the study period. Retention of ≥70% was selected as a pragmatic benchmark consistent with previous complex behavioural and digital health interventions. Retention can be particularly challenging in online interventions including digital sleep treatments, where a large systematic review reported a mean study discontinuation rate of 23% across e-health interventions [43]. Similarly, digital CBT-I studies have reported variable retention rates, including rates of approximately 66% in some online insomnia interventions [44], while retention rates approaching 80% have been reported in trials of Sleepio involving participants without cognitive impairment [33]. Given the additional challenges associated with retention in persons with cognitive impairment, a retention threshold of ≥70% was considered indicative of acceptable feasibility.Adherence rate of ≥66%, defined as completion of four out of the six sessions included in the intervention. Completion of four or more sessions has previously been used to define treatment completion in digital CBT-I studies, including trials of Sleepio where adherence approaches 80% in those with normal cognition [32]. However, as mean adherence rates in digital mental health interventions are approximately 60% [45], and because cognitive impairment may present additional barriers to sustained engagement, an adherence threshold of ≥66% was considered appropriate.Acceptability of the intervention, which will be assessed using both the System Usability Scale (SUS) [46] and Usability Metric for User Experience Lite (UMUX-Lite) [47]. The SUS is a well-established, validated, brief, ten-item Likert-scale measure designed to provide an overall assessment of perceived usability that is scored on a range from 0 to 100, with scores greater than 68/100 considered to be of average usability [46]. In this study, our target is that ≥70% of the sample will score ≥ 70/100 on the SUS as an indicator that it is usable and acceptable. The UMUX-Lite is a shorter, Likert-type instrument with two items also scored from 0 to 100 that likewise evaluates user satisfaction with a system or product to infer usefulness and usability. While there is no precise cut-off point, scores ≥ 70/100 are considered acceptable, albeit similar to the SUS; there is no strict cut-off. Hence, in this study, we will also target ≥70% scoring ≥70/100 as a marker of acceptability.Participant engagement will be assessed using objective platform metrics including the number of logins, completion of sleep diary entries, session completion rates, and overall duration of programme use. Feasibility thresholds were predefined based on published recommendations for pilot and feasibility trials and comparable behavioural intervention studies.

#### 2.6.2. Secondary Outcomes

All secondary outcomes are exploratory and will not be powered. These will be obtained in order of hierarchy according to sleep, psychological, cognitive, and functional domains:Changes in sleep, which will be assessed by the following: changes in SCI scores [38] and Insomnia Severity Index (ISI) scores [48], a validated 7-item instrument to assess self-reported insomnia severity over the previous two weeks. Scores range from 0 to 28, taking a cut-off of ≥8 as the sub-threshold for insomnia and scores ≥ 15 indicating clinical insomnia [48].Changes in psychosocial health, which will be assessed pre- and post-intervention by examining the following:
Patient Health Questionnaire 8 (PHQ-8) [49], a valid diagnostic and severity measure for depressive disorders;Generalised Anxiety Disorder 7 (GAD-7) [50], a widely-used and validated measure for assessing generalised anxiety disorder;Euroqol EQ 5D Visual Analogue Scale [51], which records subjective assessment of health-related quality of life on a 100-point vertical visual analogue scale on which the endpoints are labelled ‘the best health you can imagine’ and ‘the worst health you can imagine’;Dementia Quality of Life Instrument (DEMQOL) [52], a validated 29-item measure for assessing self-reported quality of life in people with dementia.Changes in cognition and function, which will be assessed pre- and post-intervention by the MMSE [39], CDR Scale (global score) [42], and Alzheimer’s Disease Assessment Scale—Cognitive Subscale (ADAS-Cog) [53], a validated assessment of cognition involving 11 tasks and scores ranging from 0–70, Disability Assessment for Dementia [54] (a 40-item assessment of functional ability involving personal and instrumental activities of daily living in people with dementia), and the British Columbia Cognitive Complaints Inventory (BC-CCI) [55] (a brief 6-item assessment of self-reported cognitive difficulties involving concentration, memory, articulation, thinking, and problem-solving over the previous seven days, with scores ranging from 0 to 18, with higher scores indicating greater perceived cognitive impairment).

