## 2. Materials and Methods

### 2.1. Design

REST is an investigator-blinded, randomised, controlled, two-arm, parallel feasibility study. Participants will be allocated in a 1:1 ratio to either the intervention group or a true wait-list control group through a centrally managed, computer-generated randomisation process. An asymptotic maximal randomisation strategy, with a maximum tolerated imbalance of three, will be employed. The study coordinator will not be blinded to group allocation, as this is necessary to deliver training on the intervention to participants in the intervention arm. In contrast, data collectors and controllers, statisticians, and site investigators will remain blinded to treatment assignment. Participants will be randomised in a 1:1 ratio using a computer-generated sequence. Allocation concealment will be ensured using sequentially numbered, opaque, sealed envelopes.

Baseline variables recorded will include demographic information (such as age, sex, ethnicity, employment status, and education status), lifestyle factors (such as smoking history, level of physical exercise, caffeine, and alcohol consumption), medical co-morbidities, and regular medications. The principal investigator, an attending/consultant physician, will adjudicate on medical inclusion and exclusion criteria. Assessment of outcome measures will take place at baseline and post-intervention, which will be set at 10 weeks post randomisation. Participants assigned and randomised to the intervention group will continue to receive treatment as usual in addition to the intervention described in the next section. Those assigned to the wait-list control group will be told that they will receive the intervention at the end of the 10-week study period. They will receive ‘treatment-as-usual’ during the study period.

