### 2.7. Statistical Analysis

In accordance with Consolidated Standards of Reporting Trials (CONSORT) Guidelines [56], descriptive statistics will be used to report participants’ baseline characteristics and details of participant flow, including recruitment, retention, and adherence to the intervention. Categorical variables will be described using frequencies and percentages. Regarding continuous variables, histograms and boxplots will be used to evaluate the distribution of the data and to identify any outliers or potential errors. The mean and standard deviation will be used to describe the typical value and spread in the sample but, where data is not normally distributed, the median and interquartile range will be used. All tests of significance will be two-sided and conducted at an α = 0.05 level for statistical significance.

Feasibility outcomes (e.g., recruitment rates, retention, adherence to the intervention, and data completeness) will be summarised descriptively. These outcomes will be used to inform the design and sample size estimation of a future definitive trial. Regarding the bespoke questionnaire for acceptability and usability of the intervention, frequency distributions of the categorical data in both study groups will be compared using chi-square tests or Fisher’s exact tests, as appropriate. For continuous secondary outcomes measured at baseline and post-intervention, between-group differences at follow-up will be analysed using analysis of covariance (ANCOVA) within a linear regression framework to compare changes between study groups from baseline to post-intervention with respect of the secondary outcomes. Adjustments will be made for covariates associated with the intervention and the outcome as appropriate (for example, age, sex, baseline levels of sleep disturbance, and cognitive impairment). Model assumptions will be assessed using graphical methods, including inspection of residual plots to evaluate linearity, homoscedasticity, and normality of residuals. Multicollinearity will be assessed using variance inflation factors (VIFs).

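### The CDR global score is a coarse choice for measuring 10-week change in 30 participants; a shift table, with the sum of boxes as the change measure, would serve the pilot better

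*Protocol article*

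**What the plan says.** Section 2.6.2 lists five cognition and function measures to be assessed before and after the intervention: MMSE, CDR, ADAS-Cog, Disability Assessment for Dementia and BC-CCI. For the CDR it names the summary to be used: "CDR Scale (global score"). The same section calls all secondary outcomes exploratory and unpowered.

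Section 2.3.1 uses the same instrument for entry: participants "must score ≥18 on the MMSE and ≥0.5 to 1.0 on the CDR". It describes the CDR as a "commonly-used clinician rated measure of global symptom severity and burden in persons with cognitive impairment" and does not list the score levels.

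Section 2.1 has one post-baseline assessment, "which will be set at 10 weeks post randomisation". Section 2.4 sets the size: "The target of the study is to recruit a total of 30 patients over a six-month recruitment period", and adds that "A formal sample size calculation has not been undertaken". Section 2.6.1 sets a feasibility threshold: "Retention of ≥70% of participants throughout the study period".

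Section 2.7 says that between-group differences at follow-up in continuous secondary outcomes "will be analysed using analysis of covariance (ANCOVA) within a linear regression framework". It adds mixed-effects models on all observed data and Cohen's d to inform later sample size calculations. It names no method for an ordinal score as a secondary outcome. The Limitations section says that the exploratory analyses serve mainly to guide outcome selection, sample size and design for the definitive trial.

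**The concern.** The article does not leave the CDR summary open. It picks the global score, which on usual scoring is a five-level stage. All participants would then start on one of two levels, 0.5 or 1.0, and be scored once more 10 weeks later. If few of them cross a category boundary, most change scores are exactly zero.

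Low power is common to every secondary outcome here, and the article says so. The difficulty specific to this score is that its variance and effect size are set by the few people who change. Those are the quantities that the pilot is meant to hand to the definitive trial. A flat result could also be read as the CDR being unresponsive, when only its coarsest summary had been tried.

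**Working it through.** The article gives no change rate, standard deviation or effect size for the CDR, so there is no figure of its own to reproduce. The check is a sensitivity analysis.

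**Inputs from the article:** N = 30, allocated 1:1, so 15 per arm; retention threshold 70%, so 0.70 × 30 = 21; one follow-up at 10 weeks; entry CDR 0.5 to 1.0.

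**Assumptions:** global levels 0, 0.5, 1, 2 and 3; a share p of participants changes global category by week 10, with p between 2% and 20%; participants change independently.

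**Step 1. How many change?** Expected changers = n × p. Chance that nobody changes = (1 − p)^n.

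| Assumed p | Changers, n = 30 | P(none), n = 30 | Changers, n = 21 | P(none), n = 21 |
|---|---|---|---|---|
| 2% | 0.6 | 0.55 | 0.4 | 0.65 |
| 5% | 1.5 | 0.22 | 1.05 | 0.34 |
| 10% | 3.0 | 0.04 | 2.1 | 0.11 |
| 20% | 6.0 | 0.001 | 4.2 | 0.009 |

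For example, 0.95^30 = 0.215 and 0.95^21 = 0.341.

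**Step 2. What does the variance estimate rest on?** If each change is one step of 0.5, equally often up and down, SD of change = √(p × 0.5²). This is √(0.02 × 0.25) = 0.07 at 2% and √(0.20 × 0.25) = 0.22 at 20%. The SD varies about threefold and depends only on how many people happen to change.

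**Step 3. Influence of one person.** A step of 0.5 moves a 15-person arm mean by 0.5/15 = 0.033. A step from 1 to 2 moves it by 1.0/15 = 0.067. Steps at the upper end therefore count double in a linear model.

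**Step 4. The limiting case.** If nobody changes, week-10 scores equal baseline scores exactly. ANCOVA residuals are then all zero, and a Cohen's d based on change is 0/0, so undefined. A d based on week-10 scores would only repeat the chance imbalance at baseline.

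**Step 5. Separating this from low power in general.** For any continuous outcome, the d detectable with 80% power at two-sided 0.05 is about (1.96 + 0.84) × √(2/n): 1.02 at 15 per arm and 1.25 at 10 per arm. That limit applies to all the secondary outcomes. The dependence on a few changers in Steps 1 to 4 comes from the small number of levels.

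**The case against.** A reader might infer that the entry range of 0.5 to 1.0 leaves almost no one able to change, so that the outcome is nearly uninformative by design. The article does not support that. The range is an inclusion criterion and binds at baseline only; at week 10 a participant may score within, below or above it. Nor does the article give a change rate. At an assumed 20%, four to six changers would be expected, which is few but not none.

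Three further objections have weight. First, section 2.7 ties ANCOVA to continuous outcomes and does not name the CDR there or under Cohen's d, so it cannot be said that the article assigns a linear model to the global score. It does, however, name no other between-group method for a secondary outcome. Second, the CDR is one of five exploratory cognition and function measures, beside finer ones such as ADAS-Cog (0–70) and MMSE (0–30). No conclusion depends on it, and no rule would discard it for lack of response. Third, finding that a global stage does not move in 10 weeks is itself a legitimate pilot result.

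These objections keep the point small. They do not remove it, because the choice of summary is written into the article and informing outcome selection is the declared purpose of these analyses. The score levels and the sum of boxes are general knowledge of the instrument, not statements in the article, and are treated here as assumptions.

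**Conclusion.** The point holds as a low-severity remark on a stated choice. It is neither an error nor a contradiction. Coarse scoring, a 10-week follow-up and about 30 participants together make it likely that few change category: between 0.6 and 6 of 30 over assumed rates of 2% to 20%. At 5% there is roughly a one-in-five chance that none changes, or one in three if 21 are retained. An adjusted mean difference, variance or Cohen's d from this score would be a weak guide for the definitive trial. The size depends entirely on the assumed change rate and on the usual five-level scoring.

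**What to change.** Keep the CDR global score for eligibility and staging. Report its change as a baseline-by-week-10 cross-tabulation by arm, and leave it out of the ANCOVA and the Cohen's d calculations. If the box ratings are recorded in order to derive the global score, name the CDR sum of boxes (0–18 on usual scoring) from the same interview as the CDR change outcome, analysed by ANCOVA with its baseline value as covariate. If the sponsor prefers the global score as the change outcome, one sentence should justify it and name a method suited to an ordinal score with few levels.

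The cross-tabulation costs nothing. On the stated assumption the sum of boxes needs no extra visit or test, only a sentence in sections 2.6.2 and 2.7. If only the global score is now captured, the data form would need fields for the box ratings.

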### 2.7. Statistical Analysis

In accordance with Consolidated Standards of Reporting Trials (CONSORT) Guidelines [56], descriptive statistics will be used to report participants’ baseline characteristics and details of participant flow, including recruitment, retention, and adherence to the intervention. Categorical variables will be described using frequencies and percentages. Regarding continuous variables, histograms and boxplots will be used to evaluate the distribution of the data and to identify any outliers or potential errors. The mean and standard deviation will be used to describe the typical value and spread in the sample but, where data is not normally distributed, the median and interquartile range will be used. All tests of significance will be two-sided and conducted at an α = 0.05 level for statistical significance.

Feasibility outcomes (e.g., recruitment rates, retention, adherence to the intervention, and data completeness) will be summarised descriptively. These outcomes will be used to inform the design and sample size estimation of a future definitive trial. Regarding the bespoke questionnaire for acceptability and usability of the intervention, frequency distributions of the categorical data in both study groups will be compared using chi-square tests or Fisher’s exact tests, as appropriate. For continuous secondary outcomes measured at baseline and post-intervention, between-group differences at follow-up will be analysed using analysis of covariance (ANCOVA) within a linear regression framework to compare changes between study groups from baseline to post-intervention with respect of the secondary outcomes. Adjustments will be made for covariates associated with the intervention and the outcome as appropriate (for example, age, sex, baseline levels of sleep disturbance, and cognitive impairment). Model assumptions will be assessed using graphical methods, including inspection of residual plots to evaluate linearity, homoscedasticity, and normality of residuals. Multicollinearity will be assessed using variance inflation factors (VIFs).

Analyses will be conducted according to the intention-to-treat (ITT) principle, including all participants with available outcome data in the groups to which they were randomised. Missing outcome data will be assumed to be missing at random, and no imputation will be performed for the primary analysis in this feasibility study. Mixed-effects models using all available observed data will be employed under this assumption that data are missing at random. The extent and patterns of missing data will be reported descriptively. No formal adjustment for multiple comparisons will be applied, as secondary analyses are exploratory and hypothesis-generating. Consistent with methodological recommendations for pilot studies, a sample of 30 participants is considered sufficient to estimate key feasibility parameters and generate variance estimates for a future definitive trial. Feasibility outcomes will be presented with 95% confidence intervals. Exploratory between-group effect sizes (Cohen’s d) will also be calculated to inform future sample size calculations. The overall study flow is illustrated in Figure 1.

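### The between-arm test of the acceptability questionnaire has no valid comparison group, because wait-list controls have not used Sleepio at any assessment, and the SUS target's denominator is left open

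*Protocol article*

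**What the plan says.** Three places in the protocol article bear on this.

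- **Section 2.7 (Statistical Analysis).** "Regarding the bespoke questionnaire for acceptability and usability of the intervention", the plan is that "frequency distributions of the categorical data in both study groups will be compared using chi-square tests" or, where appropriate, Fisher's exact tests. The same section says that feasibility outcomes will be summarised descriptively and presented with 95% confidence intervals. It bases analyses on participants with available outcome data.
- **Section 2.1 (Design).** The comparator is a true wait-list on usual treatment: "Those assigned to the wait-list control group will be told that they will receive the intervention at the end of the 10-week study period". Outcomes are assessed at baseline and at 10 weeks after randomisation. No later assessment of the wait-list arm is described.
- **Section 2.6.1 (Primary Outcomes).** Acceptability is a primary outcome, measured by the SUS and the UMUX-Lite. For the first, "our target is that ≥70% of the sample will score ≥ 70/100 on the SUS". For the second, "we will also target ≥70% scoring ≥70/100 as a marker of acceptability", with no denominator given. No bespoke questionnaire appears in section 2.6.

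**The concern.** A usability rating presupposes use. At baseline nobody has used Sleepio, and at week 10 only the intervention arm has. A two-group test of ratings of the programme therefore has nothing valid in its second group. If controls leave the form blank, there is no test. If they are handed the form anyway, users are compared with people judging something they have not seen.

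Two loose ends sit beside this. The analysis section names an instrument that the outcome section does not list. The outcome section sets a pass mark without saying who is in the denominator. Acceptability is one of the criteria meant to inform a definitive trial. If its denominator is settled only after the data are in, whether it was met can depend on that choice.

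**Working it through.** The article gives no calculation for acceptability, so there is no figure of the plan's own to reproduce. The check has three steps.

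**Inputs.** Total 30 (section 2.4). Allocation 1:1 and maximum tolerated imbalance 3 (section 2.1). Target proportion 70% at a score of 70 or more, and retention threshold 70% (section 2.6.1).

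**1. The between-arm test.** Take 15 Sleepio raters, 11 favourable and 4 not, and no control raters. The table is [11, 4] over [0, 0]. Each expected count is row total × column total / grand total, so both control cells are 0 × 11/15 = 0 and 0 × 4/15 = 0. The chi-square statistic Σ(O − E)²/E is then undefined. Fisher's test returns an undefined odds ratio and p = 1. The same happens for any split in the Sleepio arm, because the control row is empty.

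**2. The target, if the sample is all 30 randomised.**
- Needed: 0.70 × 30 = 21 people scoring 70 or more.
- Able to have used Sleepio by week 10: 30/2 = 15, so at most 15/30 = 50.0%.
- With an even total the arm difference is even, so an imbalance limit of 3 allows a difference of at most 2, that is 16 to 14. The ceiling is then 16/30 = 53.3%.
- If the sample instead meant everyone retained in both arms, 15 users would give 15/24 = 62.5%, 15/22 = 68.2% or 15/21 = 71.4%. With 15 in the Sleepio arm, the target would be reachable only if all users stayed, all scored 70 or more, and at least 9 of the 15 controls were lost.

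**3. The target, if the denominator is the Sleepio arm.** The count needed is 0.70 × n rounded up. The exact (Clopper-Pearson) limits for x of n are the 2.5% quantile of Beta(x, n − x + 1) and the 97.5% quantile of Beta(x + 1, n − x).

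| Sleepio arm n | 0.70 × n | Needed | Proportion | Exact 95% CI |
|---|---|---|---|---|
| 14 | 9.8 | 10 | 71.4% | 41.9% to 91.6% |
| 15 | 10.5 | 11 | 73.3% | 44.9% to 92.2% |
| 16 | 11.2 | 12 | 75.0% | 47.6% to 92.7% |

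Missing ratings matter as well. If 11 of 15 give a rating (about the 70% retention threshold), the bar among raters is 8/11 = 72.7% (39.0% to 94.0%). With non-raters counted as not meeting the target, all 11 raters would have to score 70 or more to reach 11/15.

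**The case against.** The best defence is that the faulty sentence carries little weight. Much of that stands.

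- **Is the test the only analysis of acceptability?** A reader might infer so, because it is the only analysis in section 2.7 that names acceptability. The documents do not support that. The abstract lists acceptability among the feasibility outcomes, and section 2.7 plans descriptive summaries and 95% confidence intervals for these. A proportion with its precision is already intended.
- **Does the faulty test disable the primary criterion?** No. The test is tied to the bespoke questionnaire, and the 70% targets are tied to the SUS and UMUX-Lite. Nothing in the text makes the targets depend on the test.
- **Is the SUS target impossible?** A reader might infer that too. It holds only if the sample means all 30 randomised and controls without a score count as failures. The rule on available outcome data makes that doubtful, since someone who has not used Sleepio has no valid score. The authors may well mean Sleepio users. The legend of Figure 1 defines both scales, but the figure is not shown, so their placement by arm cannot be checked.
- **Is the bespoke questionnaire just a slip for the SUS and UMUX-Lite?** That cannot be assumed. The objectives also mention overall participant satisfaction, and a separate form may exist in the full protocol.

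What the defence does not remove is the explicit plan to compare both groups on a questionnaire about an intervention that one group has not received. Nor does the text say who is in the denominator, and the two-group sentence makes a two-arm reading harder to dismiss.

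**Conclusion.** The point holds. The between-arm comparison is wrong as written: given the wait-list design and the two assessment times, it has no valid control ratings. This rests only on sections 2.1 and 2.7 and on the absence of any described assessment of controls after they receive Sleepio.

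The denominator is an ambiguity with a large possible effect, not a proven impossibility. Read as all 30 randomised, the ceiling is 50% (at most 53%) against a target of 70%. Read as the Sleepio arm, the target is attainable at 10/14, 11/15 or 12/16, with an exact interval of about 45% to 92% at 11/15. The instrument name is a mismatch to reconcile.

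This should be fixed. It concerns the wording of one primary feasibility criterion and one stray test, and leaves the design and the other feasibility outcomes untouched.

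**What to change.** 1. Delete the between-group test of the acceptability questionnaire from section 2.7.
2. In section 2.6.1, define the denominator for both the SUS and the UMUX-Lite targets as participants randomised to Sleepio. Count those without a rating as not meeting the target in the main figure, and show the proportion among raters alongside. Say explicitly that this departs from the available-data rule for this outcome.
3. Report each proportion with an exact 95% confidence interval, against at least 70% of the actual arm size and not a fixed count (for example 10/14, 11/15 or 12/16).
4. Reconcile the bespoke questionnaire with the instruments in section 2.6. If it is a separate form, list it there and describe it in the Sleepio arm only.

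The cost is wording: no extra participants, visits or data. The downside is a stricter target when ratings are missing. With 13 of 15 rating, 11 of those 13 (84.6%) must score 70 or more, and with 11 of 15 rating, all must. The figure among raters lets readers see how much of a shortfall is due to missing ratings.
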